### Outcome assessment and data collection

Outcome measurements will be evaluated at the Operative Unit of Physical and Rehabilitation Medicine of Ferrara University Hospital by the same blinded assessors at the four time points (Fig. 1): (a) baseline (prior to the first intervention session, T0), (b) intermediate (after six training sessions, T1), (c) end of treatment (after the completion of 12 sessions, T2) and (d) follow-up (after 3 months from the end of training program, T3). Before the last outcome assessment, a blinded physiotherapist will contact each participant to remind them to attend the measurements sessions. A summary of the measures to be collected is reported in Table 1. A physician member of the research team involved in the subject enrollment will administer the MMSE and all the other clinical measures (EDSS, MAS) to determine eligibility for each patient. Moreover, the person responsible for the participant selection will record the general demographic information (age, gender), comorbidities and medical history.

**Table 1 Tab1:**
[figure not shown]
Schedule of enrollment, interventions and assessments

*Abbreviations*: *T-1* enrollment, *T0* baseline, *T1* intermediate, *T2* end of treatment, *T3* 3-month follow-up, *EPC* endothelial progenitor cell, *CEC* circulating endothelial cells, *T-reg* immunological rare cell populations, *ANGPT* angiopoietin, *BDNF* Brain Derived Neurotrophic Factor, *BMP* Bone Morphogenetic Protein, *dPAPP-A* Pregnancy-associated Plasma Protein A, *EGF* Epidermal Growth Factor, *ET* endothelin, *FGF* Fibroblast Growth Factor, *FST* follistatin, *G-* granulocyte, *GM-* granulocyte-macrophage, *CSF* Colony Stimulating Factor, *HB-EGF* Heparin-binding EGF-like growth factor, *HGF* Hepatocyte Growth Factor, *IFN* interferon, *IL* interleukin, *ra* receptor antagonist, *IP-10* 10 kDa-interferon gamma-induced protein, *MCP-1* Monocyte Chemoattractant Protein 1, *MIP-1α* C-C motif chemokine 3, *MPO* myeloperoxidase, *NCAM* Neural Cell Adhesion Molecule, *PAI* Plasminogen Activator Inhibitor, *PDGF* Platelet-derived Growth Factor, *Pecam* Platelet and Endothelial Cell Adhesion Molecule, *PLGF* Placenta growth factor, *PTX* pentraxin, *RANTES* C-C motif chemokine ligand 5, *sE-Selectin* Soluble Endothelial Leukocyte Adhesion Molecule, *S-ICAM* Soluble Intercellular Adhesion Molecule, *s-VCAM* Soluble Vascular Cell Adhesion Molecule, *TF* Tissue Factor, *TNF* Tumor Necrosis Factor, *VEGF* Vascular Endothelial Growth Factor, *GSH/GSSG* reduced glutathione/oxidized glutathione ratio

### Primary outcome: gait speed

This will be assessed by the T25FW [59] a quantitative measure of gait speed, also included in the Multiple Sclerosis Functional Composite. The patient is directed to one end of a clearly marked 25-ft course and is instructed to walk 25 ft (7.62 m) as quickly as possible, but safely, using the prescribed assistive devices. The task is immediately administered again by having the patient walk back the same distance. The test will be performed according to the instructions reported on the manual of the National Multiple Sclerosis Society. To ensure an accurate measure of the primary outcome, the time needed for each subject to complete the test will be collected with the aid of a photocell system (Cronopics, Chronojump Boscosystem Technologies, Rieti, Italy) with a precision of a millisecond and simultaneously by the assessors with a chronometer. Moreover, this test will always be performed as the first outcome measure, to avoid possible muscle fatigue derived from the other test previously taken. The walking speed will be calculated as the mean of the two trials performed.

### Secondary outcome measures

A significant number of secondary outcome measures will be employed to explore fatigue, QoL, balance, walking endurance, mobility and their possible connection with brain plasticity. Secondary outcomes will include: (1) clinical measures and questionnaires, (2) hemodynamic and metabolic evaluations and (3) laboratory-based measures. Every specific measure is detailed in the following section.

### Clinical and quality of life measures

6-minute Walking Test (6MWT): walking endurance is measured with the 6MWT. This test, first validated in subjects with cardiopulmonary problems, is also considered a feasible, reproducible and reliable measure in MS [60]. Subjects will be instructed to walk up and down as far as possible on a 22-m walkway in 6 min without encouragement, with the possibility to slow down and rest if necessary. The total distance walked will be recordedBerg Balance Scale: this is an assessment scale of ability to maintain balance – statically or while performing functional movement. It includes 14 observable tasks common to an everyday life measured on a 5-point ordinal scale [61]. This scale was previously widely employed in MS subjects [62]Timed Up and Go test: the test is a combined measure of gait speed, balance, coordination and lower-limb strength. Subjects will be given verbal instruction to stand up from a chair, walk 3 m at their regular pace, cross a line marked on the floor, turn around, walk back and sit down [63]. The patients may use any gait aid that they normally use during ambulation, but may not be assisted by another person; however, a study staff member will guard the subject during the test. Subjects will perform three trials and the time it takes to perform each trial will be recorded with a stopwatch. The best trial will be consideredFatigue Severity Scale: this is a method of evaluating fatigue in MS and other conditions. Essentially, the scale consists of answering a short questionnaire that requires the subject to read each statement and rate his or her level of fatigue from 1 to 7, depending on how appropriate they felt the statement applied to them over the preceding week [64]Modified Ashworth Scale: this is a 6-point measure of spasticity; the assessor will rate the perceived amount of resistance or tone at the hip, knee and ankle flexor and extensor muscles [56]Patient Health Questionnaire: this is a questionnaire to investigate the presence of depressive symptoms as well as to characterize the severity of depression [65]. It is composed of nine items based on the frequency of occurrence in the past 2 weeks of depression symptoms and has been found to be valid also in individuals with MS [66]Short Form Health Survey: this is a generic measurement to measure health‐related QoL. It consists of eight subscales with a score ranging from 0 to 100 used separately as outcome measures of various aspects of health‐related QoL. It also measures two main health concepts: physical and mental. The questionnaire has been already employed in clinical studies involving MS subjects [67]Multiple Sclerosis Impact Scale: this is a 29‐item self‐report measure with 20 items associated with a physical scale and nine items with a psychological scale [68]. Items ask about the impact of MS on everyday life in the past 2 weeks with possible answers set on a 1-to-5 Likert scale. Each of the two scales is converted to a 0–100 scale where a score of 100 indicates a greater impact of disease on daily functionMultiple Sclerosis Walking Scale: this is a 12-item walking scale that assesses a self-report measure of the impact of MS on the individual’s walking ability [69]

### Hemodynamic and metabolic evaluations

Complete brain circulation assessment will be performed by the application of a validated model with parameters measured at the bed side by the means of an Echo Color Doppler. Subsequent post analysis permits us to obtain in-flow and out-flow measurements as well as measurements of the rate of collateral cerebral venous return [70]. Metabolic measurements will be assisted by the NIRS technology and by assessment of circulating metabolic marker (refers to Laboratory-based measures section). NIRS is a noninvasive, portable technique for the ambulatory, remote monitoring of oxygenation changes in response to motor tasks of human muscles and brain cortex. Patients enrolled in the study will undergo metabolic evaluation consisting of different measurements: assessment of muscular oxygen consumption at gastrocnemius at rest (rmVO_2_) and dynamic evaluation of cerebral activation during a simple walking task performed on a treadmill.

#### Resting muscular oxygen consumption at gastrocnemius

The muscle metabolism assessment will be performed by a continuous wave system (Oxymon MK III Artinis Medical System, the Netherlands) consisting of two channels. The measurement, already employed in MS subjects [71], is performed on gastrocnemius in a resting supine position as detailed elsewhere [72]. The absolute value of rmVO_2_ will be measured in both legs and calculated by analyzing the rate of increase in deoxygenated hemoglobin concentration during venous occlusion. The concentration changes of deoxygenated hemoglobin will be converted into milliliters of oxygen per 100 g of tissue per min. The mean value between the two legs, as well as the data for the more impaired leg, will be considered for data analysis.

#### Cerebral activation analysis during a motor task

The brain metabolism evaluation will be performed using another optical imaging system (NIRScout, NIRx Medical Technologies LLC, Glen Head, NY, USA) consisting of 16 light source fibers and 16 detector fibers, resulting in a 48-channel recording of cortical changes in oxygenated, deoxygenated and total hemoglobin. For the measurements of the present study the optodes will be tightly placed on the skull with the use of a holder cap with the interoptode distance set at 30 mm, covering the bilateral motor and premotor cortex. Patients will walk on the treadmill at a speed of 0.2 km/h assisted by personnel and with partial body weight support if needed, performing four short tasks (30 s of walking) alternated by rest periods (30 s) [73]. Data will be analyzed for possible selective changes of cerebral perfusion by specific software (NIRSlab). For each patient will be calculated the area under the curve of oxygenated, deoxygenated and total hemoglobin for each channel and hemisphere (media of the area under curve of each one of the 24 channels of selected hemisphere). Moreover, the data will also be analyzed with the software NIRS-SPM to draw a map of activation of the selected brain areas during the test and to perform a *t* test statistical comparison within subjects and between treatments, as well as other possible correlations with clinical or laboratory parameters.

### Laboratory-based measures

#### Samples processing (harvesting and storing)

Circulating biomarker analyses will be performed on blood samples collected from patients at each time point (T0, T1, T2 and T3), in fasting conditions, at the University Hospital of Ferrara. Blood collection will consist of a total of approximately 18 ml of whole blood distributed in three different test tubes (based on the analyses to be performed) containing either ethylenediaminetetraacetic acid (EDTA) or sodium citrate or ribonucleic acid (RNA) stabilizer. Once a suitable vein has been identified, the area where the needle will be inserted will be sterilized and the needle inserted. When the amount of blood extracted satisfies the study requests, the needle will be removed from the vein and a swab will be placed on the forearm. The patient must remain in a resting position for few minutes and they will be asked to communicate any adverse reaction felt. The blood samples collected will be labeled with a unique alphanumeric code identifying each participant; samples will be then packed and safely transferred to the Biobank Service of the Laboratories of the Technologies of the Advanced Therapies of the University of Ferrara. Samples collected in EDTA will be processed in real time for rare circulating cell population quantification through multiparametric flow-cytometry analyses. Samples collected in sodium citrate will be centrifuged and plasma will be collected, aliquoted and frozen at −80 °C in multiple and single-use aliquots for analysis of soluble circulating factors. Samples collected in RNA stabilizer will be used for analysis of transcriptional expression profiles. The biological samples of the participants will be catalogued and stored anonymously using the unique alphanumeric code identifying the patients, the access to samples will be restricted to the researchers involved in the RAGTIME trial.

#### Blood samples analyses

Circulating progenitor cell subsets, circulating endothelial cells and immunological rare cell populations (Treg) will be evaluated in fresh blood collected in EDTA by multiparametric flow-cytometry analyses [74, 75]Levels of glycolytic or mitochondrial activities will be obtained by analysis of the metabolic markers lactate and pyruvate and by the Glutathione Ratio. These will be determined in plasma samples by colorimetric assays [76–78]Cytokines/chemokines/growth factors, neurotrophic factors, markers of brain damage and coagulation factors will be quantified in plasma samples by multiplex immunoassay according to the manufacturer’s instructions by using specific Milliplex MAP kits (Luminex xMAP technology, Merck-Millipore, Germany) or by commercially available enzyme-linked immunochemical and immunosorbent assay following the manufacturing instructions [76, 79, 80]Additional plasma proteins, encoded by RNA selected by transcriptomic approaches [81], will be measured in plasma samples by the above reported assaysMetabolism markers (lactate, pyruvate and Glutathione Ratio) will be determined in plasma samples by colorimetric assays [82]

Additional information is reported in Table 1.

### Data management

The statistical unit will be responsible for data management (quality control and data cleaning) and data analyses according to the different research hypotheses described. A statistician will be in charge for the analysis of clinical and laboratory data, using several statistical packages such as Medcalc Software (MedCalc Software bvba, Ostend, Belgium), IBM-SPSS Statistics (IBM, Armonk, NY, USA) and Stata Statistical Software (Release 13. College Station, TX: StataCorp LP, USA). Study design and statistical plan of the study has been discussed with, and prepared by, the supporting statistical unit working at our institution.

### Sample size and power

The primary outcome for this study is to detect walking differences (specifically, T25FW measurement) between MS subjects who underwent RAGT and MS subjects who underwent CT. To calculate the sample size for this study, we used the data from a previous study [18] where a RAGT effect size of 0.40 was observed. This value is based on a decrease of values for T25FW from 8.8 ± 3.1 s at baseline to 7.4 ± 3.8 s after RAGT. Given equal allocation between treatment and control arms, 88 subjects are required to maintain a Type I error rate of 5.0 and 80% power to detect a difference between intervention groups. Conservatively, we expect a 10% rate of dropout or loss to follow-up. We will assume that dropout participants will not improve from the last measured point; thus, the sample size will be increased by 10% to 98 subjects (49 per arm).

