## Background

Multiple sclerosis (MS) is a chronic inflammatory disease causing widespread degeneration of the central nervous system. The disease, with different features and progression according to the clinical phenotype [1], gradually results in severe neurological deficits [2] with complex, variable and unpredictable patterns of symptoms [2] including different motor deficits [1]. Locomotor disability and balance disorders affect approximately 75% of persons with MS, with altered coordination of posture and gait [3, 4], mobility problems [5, 6], reduced walking competency [3] and increased risk of falling [7]. In progressive MS, the high prevalence of motor disorders and gait disabilities, the negative impact on personal activities and quality of life (QoL), and the limited effects of specific medications [8] make gait rehabilitation a crucial part of the management. The aim is to increase patients’ levels of activity and independence [9] and their QoL, even independent of symptom regression [10, 11]. Gait disabilities showed improvement following physical therapy [4, 12–14] and low-to-moderate-intensity aerobic over-ground or treadmill training, which represents a useful option for rehabilitation, also in combination with body weight support [15–17]. To this end, a robot-driven gait orthosis was recently developed, studied and considered a feasible and effective therapeutic option in MS subjects with severe walking disabilities. Robot-assisted gait training (RAGT) allows a more effective support of walking movements and imitation of a nearly normal gait pattern during treadmill training at a higher speed, with improvements in walking distance, velocity and knee extensor strength compared to conventional therapy [18, 19]. Several studies have tested in samples of MS patients the effects of interventions, such as treadmill training [4], bodyweight-supported training on a treadmill [20, 21], RAGT [18, 19, 22–26], or both treatments combined within a single session [27], reporting small but positive effects on functional status [4, 18–20, 23–26] or QoL [10, 21]. Recently, improvements were reported in the 6-min Walking Test and in the balance domain after RAGT [25] but not in gait speed measured by the 10-m Walk Test [26]. Unfortunately these studies, using different devices and training protocols (12 to 15 sessions over 3–6 weeks), including heterogeneous MS subgroups with a limited number of subjects and a wide range of gait disabilities (Expanded Disability Status Scale, EDSS 3–7.5), failed to offer an exhaustive evidence of the superiority of RAGT over other specific gait trainings, so larger trials are necessary [28]. Otherwise, this might be partially explained by the fact that the rehabilitation process in MS subjects is complex and person-specific [28] as the response to treatments regarding neuronal plasticity is highly individual. Functional recovery in MS is achieved by repair of damage through remyelination, with resolution of inflammation and functional reorganization. Evidence from brain systems supports an adaptive role for neuroplastic changes in MS despite its widespread pathology. Specifically, it may limit the negative effects of MS on behavior [29–32] and differs between patients and various disease types, with lower response according to patient age and disease duration [33, 34]. Moreover, different rehabilitation treatments might switch on different adaptive response. High-intensity interventions might be more effective on neural reorganization and motor recovery involving synaptic transmission and formation of novel synapses, cortical reorganization and induction of neurogenesis limited to the site of injury or involving distant healthy brain regions [35]. The effects of neuroplasticity-based technologies and interventions, virtually beneficial for functional recovery, have been poorly tested so far. Different tools, such as positron emission tomography and functional magnetic resonance imaging, could be appropriate to evaluate such recovery-related processes. Several studies have employed these techniques, revealing that in MS patients a decreased hemispheric lateralization [32] and an increasingly bilateral activation, even for simple motor tasks involving higher-control sensorimotor areas, were observed [36, 37]. Other noninvasive, reliable and less expensive measurements, such as transcranial magnetic stimulation and near-infrared spectroscopy (NIRS), could also be useful. In a NIRS-based study the coherence, considered a potentially useful marker in disorders with white matter damage or axonal loss, was found to be similar in MS subjects and controls in the resting phase, but significantly decreased during motor tasks [38]. Moreover, relevant information to identify patterns of recovery in MS patients could be added by the measurement of molecular regulators of neuronal or vascular plasticity. These biomarkers derived from blood tests include circulating cell subsets and soluble factors measurable in plasma. Previous studies involving MS subjects showed that the *N*-acetylaspartate concentration correlated with an increased lateralization index; neurotrophins that regulate neural plasticity, such as brain-derived neurotrophic factor (BDNF) [39], were found in lower concentrations compared to healthy subjects [40]. Furthermore, inflammatory cytokines, such as interleukin-1β, negatively interact with BDNF and amyloid-β has been observed in multifocal MS lesions [41, 42]. Finally, growth factors participate in neural cell survival and tissue repair processes [43–45] and, in particular, platelet-derived growth factor decreases with disease duration, being low in primary progressive MS patients [46] while incomplete glucose oxidation by glycolysis and mitochondria results in increased oxidative stress that promotes lesion progression rather to repair [47–49]. Also, disturbances of the hemostatic mechanisms, which are closely and reciprocally related to inflammation, are relevant for neurological disorders, in particular procoagulant factors and receptors, as well as main anticoagulant proteins endowed with anti-inflammatory activities, that exert cytoprotective effects and favor endothelial barrier stabilization, neurogenesis and angiogenesis [50]. Lastly, besides soluble factors, growing evidence advances the concept that stem cells can modulate nervous system action as well as the dysregulation of inflammatory responses and immune self-tolerance has to be considered a key element in the autoreactive immune response in MS. To this end, circulating stem/progenitor cells capable of homing in on neovascularization sites [51], and regulatory T-cells (Treg) have emerged as crucial players in the pathogenic scenario of autoimmune inflammation with a role in their modulation by pharmacological and rehabilitation therapy.

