### Statistical analyses

Standard methods for the analysis of randomized controlled trials will be employed. Firstly a comparison of baseline characteristics of the two groups will be compared for demographics, primary and secondary outcome measures. Though our starting hypothesis called from a superiority of RAGT with respect to CT, to allow for the chance that participants enrolled in the CT group could have better outcomes than those in the intervention arm, we will use two-tailed tests of significance for all analyses. A *p* value of 0.05 will be considered statistically significant.

For the primary hypothesis, a two-way repeated measure analysis of variance (factors: treatment, time) will be run to compare differences in gait speed within the RAGT and CT groups at baseline, after treatment and follow-up. Given the large number of planned secondary outcomes, in order to reduce the probability of a false positive result, for these specific analyses the significance level will be fixed at 0.01.

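### The planning effect of 0.40 is the uncontrolled before-after change in the RAGT arm, so the 80% power for RAGT versus CT silently assumes that CT patients do not change

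*Protocol article*

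**What the plan says.** All places are in the protocol article.

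- **Sample size and power, aim.** The trial is to detect walking differences "between MS subjects who underwent RAGT and MS subjects who underwent CT", and the claim is "80% power to detect a difference between intervention groups".
- **Sample size and power, effect.** The input comes from a previous study "where a RAGT effect size of 0.40 was observed", and the section explains that this value is "based on a decrease of values for T25FW from 8.8 ± 3.1 s at baseline to 7.4 ± 3.8 s after RAGT". It gives no change under CT and no difference between arms.
- **Sample size and power, result.** "88 subjects are required to maintain a Type I error rate of 5.0 and 80% power" (the 5.0 is evidently 5%). The total is then raised to 98 for 10% dropout.
- **Active control group (CT).** Each session includes around 40 minutes of over-ground walking, in bouts continued to a perceived exertion of 8 out of 10.
- **Intervention.** Both arms have twelve two-hour sessions, and the second hour (stretching and strengthening) is the same for both.
- **Background.** "Gait disabilities showed improvement following physical therapy".
- **Statistical analyses.** Tests are two-tailed because CT might do better than RAGT. The primary analysis is a treatment-by-time repeated-measures analysis of variance "to compare differences in gait speed within the RAGT and CT groups".

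**The concern.** A change from baseline within one arm contains everything that moves the outcome over the training period: the specific effect of the robot, the effect of any gait training, practice on the test, and regression to the mean. A randomised comparison removes whatever the two arms share. Using the within-arm change as the between-arm difference therefore assumes that nothing is shared, that is, that mean change under CT is zero.

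That is hard to reconcile with this design. The control arm trains the same function at substantial effort, and half of each session is identical in both arms. If CT patients improve at all, and RAGT patients improve by the cited amount, the true difference is smaller than the planning effect and the power is lower than stated. A reader of the eventual result would then credit the trial with more ability to detect a difference than it has.

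**Working it through.** **Inputs.** From Sample size and power: means 8.8 s and 7.4 s, SDs 3.1 s and 3.8 s, equal allocation, 5% error rate, 80% power, 88 evaluable, 10% dropout. From Statistical analyses: two-sided tests. The change under CT is not given, so it is treated below as an assumed share of the RAGT gain.

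**1. Reproduce the 0.40.** The change is 8.8 − 7.4 = 1.4 s. The pooled SD is √((3.1² + 3.8²)/2) = √12.025 = 3.468 s. The ratio is 1.4/3.468 = 0.404. The stated 0.40 is thus the before-after change in the RAGT arm over the pooled before and after SD. No CT figure enters it.

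**2. Try to reproduce the 88.** For two independent groups at an effect of 0.40, n per arm = 2 × (1.960 + 0.842)²/0.40² = 98.1, so 99 per arm or 198 in total. The 88 does not follow directly. It corresponds to an effect of 2.802 × √(2/44) = 0.597. It would also fit the full 1.4 s as a between-arm difference if the pre-post correlation were about 0.79 with change scores, or about 0.74 with baseline adjustment. No correlation is stated. The step to 98 reproduces: 88/0.9 = 97.8. Whether 88 follows from 0.40 is a separate question. Under every reading that yields 88 here, the effect still contains no allowance for change under CT.

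**3. Isolate the effect of a CT gain.** Grant the sponsor that 88 gives exactly 80% power for the full 1.4 s. The standardised distance of the test statistic is then 1.960 + 0.842 = 2.802. If CT achieves a share *s* of the RAGT gain, and the variance is unchanged, the distance becomes 2.802 × (1 − *s*) and power is Φ(2.802 × (1 − *s*) − 1.960).

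| Assumed CT gain | Between-arm difference | Distance | Power | Evaluable N for 80% power, 88/(1 − s)² |
|---|---|---|---|---|
| 0 | 1.40 s | 2.802 | 80% | 88 |
| 25% (0.35 s) | 1.05 s | 2.101 | Φ(0.141) ≈ 56% | about 157 |
| 50% (0.70 s) | 0.70 s | 1.401 | Φ(−0.559) ≈ 29% | 352 |

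**4. Check that this does not depend on the 88.** Use 99 per arm, the number that an effect of 0.40 requires. An effect of 0.30 gives 0.30 × √(99/2) = 2.111, hence power of about 56%. An effect of 0.20 gives 1.407, hence about 29%. The loss is the same, so correcting the arithmetic of N would not remove it.

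**The case against.** The best defence is that nobody knows what CT will achieve in this population. The Background sentence on physical therapy gives no amount and is not specific to progressive disease at EDSS 6 to 7. A zero CT change is one possible planning value, and the 25% and 50% shares are the reviewer's. This stands as far as it goes: the shares are illustrations, and the documents cannot choose between them. It does not rescue the statement in the protocol, which never says that zero was assumed and attaches 80% to a comparison for which it offers no comparative figure.

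Four stronger readings are tempting and should not be drawn.

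- **Lower power figures.** Putting effects of 0.30 and 0.20 into an unadjusted comparison with 44 per arm gives about 29% and 16%. Those figures also absorb the unexplained step from 0.40 to 88, because even with no CT gain that calculation gives only 47%.
- **A detectable difference larger than the whole cited gain.** With 44 per arm and an unadjusted SD of 3.468 s, the exact-t multiplier of 0.604 gives 0.604 × 3.468 = 2.09 s. This has the same flaw and ignores the planned repeated-measures and change-score analyses. At assumed correlations of 0.7 and 0.8, change scores (SD of change 2.749 s and 2.281 s) give 1.66 s and 1.38 s. Baseline adjustment (3.468 × √(1 − r²)) gives 1.50 s and 1.26 s. The claim reverses within a plausible range.
- **A ready-made figure in the cited study.** The Background cites the same source, jointly with another, for gains relative to conventional therapy. That does not show that it reports a usable between-arm T25FW difference, and the protocol quotes none.
- **Seconds against speed.** Planning is in seconds and the outcome is named gait speed, so the standardised effect need not carry over. The sample-size section itself specifies the T25FW measurement, however, and the direction of any shift cannot be settled without a distributional assumption. This is a point of wording, not evidence of lost power.

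**Conclusion.** The point holds in this form: the planning effect is an uncontrolled change in the RAGT arm, it is used to claim power for RAGT versus CT, and it implies zero mean change under CT, against the protocol's own description of the control. Even if 88 is accepted as giving 80% power for the full 1.4 s, power is about 56% with a CT gain of a quarter of the RAGT gain and about 29% with a gain of half.

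These figures rest on the assumed CT shares, a RAGT gain equal to the cited one, unchanged variance, a normal approximation and a two-sided 5% test. They do not depend on whether 88 follows from 0.40.

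A reader might also infer that the protocol would take a non-significant result as equivalence. It does not: the stated hypothesis is superiority, tested two-sided, so nothing needs correcting there. The finding concerns an overstated power claim and does not invalidate the design or the analysis. It should be corrected.

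**What to change.** Keep N = 98. In Sample size and power:

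1. Restate the planning effect as a between-arm difference on one named scale, either T25FW time or gait speed, matching the primary analysis.
2. Write out the mean change assumed under CT, and say that it is an assumption if no source for it is at hand.
3. Replace the single 80% figure with power for CT gains of 0, 25% and 50% of the RAGT gain, calculated for the planned analysis and with the assumed pre-post correlation stated.

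If the sponsor can justify 80% for the full 1.4 s with 88 evaluable patients, the three entries are about 80%, 56% and 29%. Otherwise they must be recalculated from the stated correlation.

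The cost is a change of wording and a short recalculation. Recruitment, interventions and assessments are untouched. The downside is that the stated power becomes less favourable.

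### The stated inputs (effect 0.40, two-sided 5%, 80% power, equal arms) do not give 88 patients; 88 needs a within-patient correlation that the protocol does not state

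*Protocol article*

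**What the plan says.** The section *Sample size and power* names the Timed 25-Foot Walk (T25FW) difference between robot-assisted gait training (RAGT) and conventional therapy (CT) as the target. For the effect it says "we used the data from a previous study [18] where a RAGT effect size of 0.40 was observed", and traces this to "a decrease of values for T25FW from 8.8 ± 3.1 s at baseline to 7.4 ± 3.8 s after RAGT". It then concludes "Given equal allocation between treatment and control arms, 88 subjects are required to maintain a Type I error rate of 5.0 and 80% power", the power being that to detect a difference between the two groups. The total is raised to 98 (49 per arm) for 10% dropout.

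The section *Statistical analyses* states "we will use two-tailed tests of significance for all analyses" and names a two-way repeated-measures analysis of variance (treatment, time) for the primary hypothesis. Under *Additional statistical analysis*, between-group tests of score change are added, and analysis of covariance is reserved for the case where the arms differ at baseline. The article gives no within-patient correlation, no SD of change and no expected change under CT.

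**The concern.** The paragraph presents 88 as following from the effect size, error rate, power and allocation that it lists. A standardised difference of 0.40 is modest, and 44 per arm is far fewer than it normally requires. The source of 0.40 adds to the doubt, because it is a before-after change in one arm and not a contrast between arms.

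At stake is the power claim for the primary outcome. The *Background* criticises earlier trials for limited numbers and inconclusive evidence of superiority. If this trial is null, readers will rely on the 80% to conclude that RAGT has no worthwhile advantage, and the stated inputs do not support that reliance.

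**Working it through.** **Inputs.** Effect 0.40 from means 8.8 and 7.4 s and SDs 3.1 and 3.8 s; type I error printed as 5.0, read as 5%; power 80%; equal arms (all from *Sample size and power*). Two-sided tests (*Statistical analyses*).

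**What reproduces.**
- Pooled SD = √((3.1² + 3.8²)/2) = 3.47 s, and (8.8 − 7.4)/3.47 = 1.4/3.47 = 0.404. So 0.40 is a Cohen's d on the raw SD, taken from a before-after change.
- Dropout: 88/0.9 = 97.8, rounded up to 98.

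**What does not reproduce: 88.** Normal approximation, n per arm = 2(1.960 + 0.842)²/d² = 2 × 7.849/d².
- d = 0.40: 15.70/0.16 = 98.1, so 99 per arm (198). The t test gives 99.1, so 100 per arm (200).
- Power at d = 0.40 (t test): 45.8% with 44 per arm, 50.0% with 49 per arm.
- d = 0.60: 15.70/0.36 = 43.6, so 44 per arm, or 88. By the t test, 44 per arm detect d = 0.604 with 80% power; 0.604 × 3.47 = 2.1 s.

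**Other readings of the stated inputs.**

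| Reading | Total patients |
|---|---|
| One-sided, d = 0.40 | 156 |
| d = 1.4/3.1 = 0.45, two-sided / one-sided | 154 / 122 |
| d = 1.4/3.8 = 0.37, two-sided | 232 |
| Single-sample (paired) test, d = 0.40 | about 51 |
| 0.40 read as Cohen's f, two groups | about 51 |

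None gives 88.

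**Adding an assumed within-patient correlation r.** With baseline adjustment the effective d is 0.40/√(1 − r²). For change scores it is 1.4/√(3.1² + 3.8² − 2r × 3.1 × 3.8). Power with 44 per arm, two-sided 5%:

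| r (assumed) | Effective d, adjusted | Power | SD of change (s) | Effective d, change | Power |
|---|---|---|---|---|---|
| 0.5 | 0.46 | 57% | 3.50 | 0.40 | 46% |
| 0.6 | 0.50 | 64% | 3.15 | 0.44 | 54% |
| 0.7 | 0.56 | 74% | 2.75 | 0.51 | 66% |
| 0.8 | 0.67 | 87% | 2.28 | 0.61 | 81% |

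Baseline adjustment reaches 80% at r of about 0.75. Change scores give about 80% at r of 0.78 (equal SDs) to 0.79 (SDs 3.1 and 3.8).

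**A route at low correlation.** For the group main effect in a repeated-measures ANOVA with f = d/2 = 0.20, the noncentrality is f² × N × m/(1 + (m − 1)r), with m visits.
- m = 4, r = 0.25: 0.04 × 88 × 4/1.75 = 8.05, power 80.1%.
- m = 3, r = 0.15: 0.04 × 88 × 3/1.30 = 8.12, power 80.5%.

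This model lets the arms differ equally at every visit, baseline included. Randomisation makes the expected baseline difference zero, so it is not a valid power model here.

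**Within-arm effect used between arms.** Taking 0.40 as the difference between arms sets the CT change to zero, although CT is an active gait-training programme. If CT improvement brought the net difference to 0.30 (assumed, for illustration), the same unadjusted test with 44 per arm would have 29% power.

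**The case against.** The strongest objection is that the two-sample comparison is not the planned primary test. The protocol names a repeated-measures ANOVA that includes baseline, and that analysis can have more power than a single post-treatment comparison. This stands. A reader might infer that the trial's power is 46%, close to a coin flip; the documents do not support that. The 46% belongs to the stated inputs taken as a simple two-arm comparison. Power under the planned analysis depends on a correlation that is not given.

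A reader might also infer that 88 is attainable only with a high correlation. That is not so, since the group main-effect calculation reaches it at 0.15 to 0.25. That calculation does not suit a randomised trial with a baseline visit, and it too needs an unstated correlation.

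It can be said that a journal article condenses the full plan, and that the correlation may be recorded there. This does not save the text. The article chose to publish the calculation and presents 88 as following from the inputs it lists.

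Finally, nothing in the documents supports 0.60 or 2.1 s as an expected or relevant difference. This also stands: 0.60 is only what 44 per arm can detect. The 2.1 s rests on the earlier study's SDs, and the *Background* says earlier trials covered EDSS 3 to 7.5, whereas this one enrols EDSS 6 to 7.

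**Conclusion.** Wrong as written. With d = 0.40, two-sided 5%, 80% power and equal arms, about 200 evaluable patients are needed, not 88. The same inputs give 44 per arm about 46% power, and 50% if all 98 are evaluable. The figure of 88 stands only if an unstated within-patient correlation is added.

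Over assumed correlations of 0.5 to 0.8, power with 44 per arm runs from 57% to 87% with baseline adjustment and from 46% to 81% for change scores. The more favourable, baseline-adjusted column is not the planned primary analysis. All these figures treat the within-arm 0.40 as the difference between arms, so any improvement under CT would lower them.

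The finding is that the stated inputs do not support the claimed power. It is not shown that the planned analysis lacks 80% power, nor that more patients must be recruited.

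**What to change.** Keep 98 patients and restate the power in *Sample size and power*.

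1. If 88 came from a repeated-measures, change-score or baseline-adjusted calculation, name that analysis, state the correlation assumed and its source, and give power over a range such as the one tabulated above. The calculation should not assume a difference between arms at baseline.
2. If no correlation was used, state that 44 evaluable patients per arm give 80% power (two-sided 5%) for a between-arm standardised difference of 0.60, about 2.1 s on the earlier study's SDs, and about 46% for 0.40. Present 0.60 as the detectable difference, not as an expected one.
3. In either case, say that 0.40 is a before-after change within the RAGT arm, and that using it between arms assumes no improvement under CT.

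The cost is wording and, unless a high correlation can be justified, a less favourable stated power. No patients, visits or procedures are added.
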